### Simulation

To determine the timing of the interim analysis, simulations of the study design were performed. Hypothetical results were drawn equal to the number of participants (50) from separate normal distributions of fixed effect sizes ranging from *d* = 0 (null) to *d* = 1.6 were subject to an emulated interim analysis after a varying number of participants had been ‘recruited’. A t-test was performed comparing the two sets and considered successful where a significance level α <  = 0.05. This was repeated 10,000 times for each combination to evaluate the effect of participant numbers on the number of trials that would either have: (1) Been prematurely halted, where an effect would have been observed had the trial completed (False Negative, type 2 error); or (2) Been incorrectly continued, where an effect was too small to be observed with confidence at the end of the study (False Positive, type 1 error).

### Data analysis

The hypothesis test at interim and final analysis will be performed using a two-sided independent t-test. The type-1 error is controlled using the O'Brien-Fleming alpha spending method for the primary outcome measure, the heat pain threshold. Other QST variables will only be analysed at the final analysis. All other comparisons between available groups will be treated as exploratory. The genotype of the individuals will also be considered to qualify the association of SNP to any observed effect.

### Data access statement

Data collected as part of this study will be available on request to the ALSPAC executive committee ([contact]). The ALSPAC data management plan (available here: http://www.bristol.ac.uk/alspac/researchers/data-access/) describes in detail the policy regarding data sharing, which is through a system of managed open access. Code used both in the work presented herein and in the statistical analysis itself will be made available from the corresponding author on reasonable request.

## Discussion

This study will utilise detailed sensory testing within a recall-by-genotype framework [11] to assess variation in pain sensitivity in healthy young adults due to commonly occurring SNPs in *TRPA1*. Importantly, this study advances the RbG approach via a novel pairing with an adaptive design using interim assessments. Our primary rationale for this approach is for deep phenotypic screening of minor allele carriers where it is difficult to estimate the effect size. By performing interim assessment our approach reduces futile assessment of participants when an effect is unlikely to be observed given a predetermined sample size and reduces excessive assessment of participants where there is a large effect.

### Comparison with standard designs

In this study we focused on the heat pain threshold (HPT) of QST as TRPA1 has been implicated in detection of thermal stimuli. The number of participants to recruit for a RbG study is typically calculated from the expected effect size of the variant, however, there is little reliable data upon which to base an effect size calculation for these *TRPA1* SNPs. When an effect size is unknown, an alternative approach is to use estimates of the minimum clinically relevant change. In a reference population, the HPT is 42 ± 2.5 °C (mean ± SD) [44] and we consider a 1.5 °C (*d* = 0.6) change in HPT as being a minimum clinically relevant change (Baron, Maier [45]). In a classic design the number of individuals required for the study can be calculated given a desired probability of observing the effect size at a defined error cut-off. In a standard RbG study design investigating a single minor allele 45 subjects (90 total) would be required in the minor and major allele groups with 80% likelihood of observing an effect at alpha <  = 0.05.

### Efficacy

The estimated effect size is commonly used to determine the number of participants to recruit for a study, however if the estimated mean effect size is lower than the actual mean effect within the sampled population then more participants will be recruited than is required to observe the effect. If we consider where we observe a large 4 °C change in heat pain threshold, a recall by genotype would have an 80% chance of observing this effect after the first seven participants per group (given our expected standard deviation 2.5 °C), however the full cohort would still have been recruited. In our study, there is a 77.6% chance of observing a 4 °C change at the first interim with fifteen participants per study arm resulting in less assessment of individuals with a hypersensitivity to noxious stimuli.

### Futility

Conversely, there is a chance that the actual mean effect within the sampled population is considerably smaller than the estimated mean effect size. In the classic design this will only be apparent once the full cohort is assessed. Using this adaptive design it is likely that the recruitment of the allele would be stopped at an interim assessment after only 30 participants are recruited. As such, our design reduces the burden on the experimenter and the participants when an effect is unlikely to be observed.

In many studies the sample size is restricted due to practical and financial concerns which can result in the study being of insufficient power to observe clinically relevant changes. In this study we have been resourced to recruit a total cohort of 100 participants where the adaptive design can screen up to 3 cohorts and is powered to detect changes of 1.43 °C (d = 0.57), 1.55 °C (d = 0.62) and 1.7 °C (d = 0.68) at each interim respectively. An analogous, “classical” RbG with multi-armed assessment with 25 participants per group would be powered to detect a difference of 2.03 °C (*d* = 0.81 α <  = 0.05) in the heat pain threshold.

### Statistical considerations

Unblinded assessment of effect size at interim has the potential to impact the final statistical analysis. For example, if an interim analysis performs a hypothesis test to reject the null hypothesis then it introduces a testing multiplicity which will increase the likelihood of type 1 errors (false positives) in the final analysis. A common approach to take account of the interim assessment is to split the alpha criteria across the additional interims, referred to as alpha spending. In its simplest form the critical value threshold is divided equally amongst the interims including the final analysis [46]. For example, the addition of an interim analysis with a desired final alpha of 0.05 results in an adjusted alpha threshold of 0.025 at the interim and final analysis stage giving an equal weight to both analyses. More commonly, alpha spending strategies which consider the available information at the time of interim assessment are employed such as the O’Brien–Fleming method, which divides the alpha threshold by the number recruited at interim relative to the total number of participants [42]. In the case where a single interim is performed after half of the participants are recruited the effect is the same as the Pocock adjustment. However, where the interim occurs with less than half, a larger effect size is required to stop for efficacy than at the end of the study which accounts for the lower confidence associated with the fewer participants earlier in the study. We opted for the O’Brien-Fleming approach as we desired to perform interim at an early timepoint to allow screening of more alleles; we expect small effect sizes and therefore will only stop for efficacy at interim where the effect is very robust; and desire the interim to have minimal impact on the final analysis.

### Simulations

The optimal point (number of participants) at which to perform the interim analysis is determined by statistical and practical considerations with the objective of making effective use of the scarce and valuable resource of the available cohort, in our case ALSPAC. Ideally, at interim, the distributions of the data should be representative of the final distribution; if not it may lead to an incorrect decision to continue or halt the experiment. We undertook simulations of the study design to better estimate this optimal interim point. We examined a broad range of possible effect sizes, but chose to focus on the characteristics under the null effect (d = 0) and the minimal clinically relevant effect size (d = 0.6). Assessment of the modelling demonstrates that an interim analysis after 15 participants per group using a confidence threshold of 80% would adequately balance this risk, whilst still allowing multiple alleles to be tested. As can be seen from Fig. 3, with 15 participants per group, we can be more than 80% confident that we will correctly halt approaching 90% of “negative” trials balanced against the risk of incorrectly halting approximately 10% of “positive” trials. Further increasing the number at interim beyond 15 had little impact on the efficiency of the interim assessment. As our sample size is fixed by available resource and statistical power is determined from effect size and sample size, then here the effect size will determine the result of the interim assessment.

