**Fig. 3 Fig3:**
[figure not shown]
Simulations of the interim analysis. **A** The number of correct interim decisions—where an interim was stopped where there was no significant finding or continued for effect sizes of 0 and 0.6. Error bars indicate 95% confidence intervals generated by bootstrapping the simulation results sampling 100 results 1000 times. **B** The change in mean % correct interim decisions as more subjects are added to interim. The interim number 15 was chosen as the relative benefit of adding more decreases above this point. **C** The effect of number of subjects on overall interim pass rate. This figure displays the % of interims that would go on to recruit a full study from populations of fixed effect sizes

If the interim analysis predicts >  = 80% statistical power using an estimated effect size then a hypothesis test will be performed using O’Brien-Fleming alpha-spending criteria:If the null hypothesis cannot be rejected at this point then recruitment of this minor allele group along with the control group will continue to the end of the planned cohort.Else if the null hypothesis can be rejected then this minor allele group will stop. The study will continue with recruitment of the next planned minor allele group.If the interim analysis predicts < 80% statistical power then recruitment of this minor allele group will stop and individuals from next minor allele group will be recruited. Recruitment will again be continued up to the pre-specified interim analysis (repeat analysis step (1))

This process will be repeated iteratively until the full cohort has been assessed (N = 100) as directed by the recruitment plan (see Fig. 2).

The interim and final analyses will use data from the Control group as the comparator therefore, to maintain equally sized groups at the end of the study and to maintain study group masking, the rate of recruitment into the Control group will reduce after each adaptation in minor allele group recruitment. The changes in recruitment strategy will be directed by the interim analysis committee and implemented by an independent group within the ALSPAC participant recruitment team.

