In the event of all minor alleles being underpowered for differences in heat pain threshold, as determined by the interim assessments, additional endpoints derived from the secondary measures (QST and flare) will inform the final group recruitment (see Fig. 3 and Table 2 which illustrate the adaptive design and its effects upon recruitment).

**Table 2 Tab2:** Interim analyses

Interim analysis #	Futility effect size	Efficacy cut-off alpha	Effect size req. for statistical eff (ΔHPT)
1	0.57	0.0013	1.63 (Δ4.1 °C)
2	0.62	0.0023	1.52 (Δ3.8 °C)
3	0.68	0.0055	1.42 (Δ3.5 °C)

Each row indicates the study state at subsequent interims. Effect sizes are displayed as Cohen’s d $$\frac{{\left( {\mu_{minor} - \mu_{major} } \right)}}{\sigma }$$ where µ is the mean and σ is the standard deviation. The futility effect size cut-off is the minimum effect size required to continue the group in the study. The futility effect size is calculated as the smallest effect size observable at the final analysis at 80% probability given an alpha cut-off of 0.05. The efficacy cut-off alpha is the alpha criteria for the interim analysis to determine efficacy. The efficacy cut-off alpha is calculated using an O’Brien-Fleming alpha spending through the gsdesign R package. With subsequent interims the alpha threshold is relaxed as the proportion of information known at interim increases due to the fixed sample size of 15. The effect size required for statistical efficacy (HPT) indicates the minimum effect size (cohen’s d) likely to be observed at 80% power at interim with the corresponding changes in HPT (Δ) indicated assuming σ = 2.5. HPT, heat pain threshold

We will follow the applicable Food and Drug Administration (FDA) guidelines for adaptive trial design [43]. To maintain the integrity of the sampling frame through this experiment, the analysis script is stated a priori and researchers involved in the data collection will not be aware of the outcomes of any interim analysis nor changes in the recruitment strategy; and therefore remain blind to genotype throughout.

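### The interim at 15 per group is said to halt about 10% of positive trials wrongly; at the effect the article focuses on (d = 0.6) the stated rule halts about 46%, or 40% of those that would have finished significant.

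*Protocol article*

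**What the plan says.** The Discussion (Simulations) says a broad range of effects was examined but that the authors "chose to focus on the characteristics under the null effect (d = 0) and the minimal clinically relevant effect size (d = 0.6"). For 15 per group it reports that close to 90% of negative trials are correctly halted, these "trials balanced against the risk of incorrectly halting approximately 10% of" positive trials. Neither label is given a number in that sentence. The Fig. 3 legend names the same two effects, 0 and 0.6, and adds: "The interim number 15 was chosen as the relative benefit of adding more decreases above this point".

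The rule is set out under Interim assessment strategy. If the interim "predicts < 80% statistical power then recruitment of this minor allele group will stop". The Table 2 footnote restates this as a cut-off on the observed effect: "The futility effect size cut-off is the minimum effect size required to continue the group in the study". The cut-offs are d = 0.57, 0.62 and 0.68 at interims 1, 2 and 3. The Discussion (Futility) describes the design as "powered to detect changes of 1.43 °C (d = 0.57") at interim 1, with the corresponding larger changes at the later ones.

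The Methods section Simulation gives 50 participants per group, normal data and a final t-test at 0.05. It defines a false negative as a trial stopped at the interim that would have shown an effect if completed.

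**The concern.** The cut-off of 0.57 is the effect detectable with 80% power at 50 per group, and the smallest effect of clinical interest is 0.6. When the true effect lies almost on the cut-off, the observed effect falls below it nearly half the time. A false-halt rate of 10% at d = 0.6 cannot come from such a rule.

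The two halting rates are the numerical balance offered in support of 15 per group. If the second is wrong, the interim committee and readers will give a futility stop more weight than it deserves. An allele with a clinically relevant effect could be dropped close to half the time while the article puts the risk at one in ten. The article also recommends the design for reuse in other recall-by-genotype studies, so the figure may be carried forward.

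**Working it through.** **Inputs, all from the protocol article**
- Interim size: 15 per group (Interim assessment strategy; Discussion, Simulations).
- Cut-offs: 0.57, 0.62, 0.68 (Table 2).
- Final size in the simulation: 50 per group, normal data (Simulation).
- Test: two-sided independent t-test at 0.05 (Data analysis; Simulation).
- SD of heat pain threshold: 2.5 °C, so 1.5 °C is d = 0.6 (Comparison with standard designs).

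**The article's other figures reproduce.** The effect detectable with 80% power at two-sided 0.05 is 0.566 at 50 per group, 0.619 at 42 and 0.679 at 35, against the stated 0.57, 0.62 and 0.68. The size for d = 0.6 comes to 44.6, so 45 per group, as stated. The chance of detecting 4 °C at interim 1 comes to 77.6%, as stated. The model used here is therefore the article's own.

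**Halt probability.** With n per group, observed d = t × √(2/n), where t has 2n − 2 degrees of freedom and noncentrality δ√(n/2). For n = 15, √(15/2) = 2.739 and there are 28 degrees of freedom. A trial halts if |t| < cut-off × 2.739.

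At interim 1 the limit for |t| is 0.57 × 2.739 = 1.561.
- δ = 0: P(|t| < 1.561) = 87.0%. This agrees with the stated figure of nearly 90%.
- δ = 0.6: noncentrality 0.6 × 2.739 = 1.643, and P(|t| < 1.561) = 46.2%. With the unrounded cut-off it is 45.7%. Using the signed difference instead of its absolute value gives 46.3%.

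**On the article's own false-negative definition.** Simulating 100,000 trials at δ = 0.6 (50 per group, interim at the first 15 per group):
- significant at the end, if all were completed: 84.5%
- halted, and would have been significant: 34% of all trials
- halted among those that would have been significant: 0.34 / 0.845 = 40%
- continued and significant: 51%, against 84.5% without the interim

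**All three stages, 15 per group at each interim**

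| Interim | Cut-off | Halted at d = 0 | Halted at d = 0.6 |
|---|---|---|---|
| 1 | 0.57 | 87.0% | 46.2% |
| 2 | 0.62 | 89.9% | 51.5% |
| 3 | 0.68 | 92.7% | 57.7% |

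**Can any cut-off at 15 per group give both stated rates for d = 0 and d = 0.6?** No.
- Halting 90% of nulls needs a cut-off of about 0.62, which halts 51–52% at d = 0.6. A one-sided rule that halts 90% of nulls still halts 37%.
- Halting only 10% at d = 0.6 needs a cut-off of about 0.17, which halts only 35% of nulls.
- With the stated 0.57, a 10% halt rate is reached only at a true d of about 1.04, that is 1.04 × 2.5 = 2.6 °C.

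**Does the interim size matter?** Hardly, at d = 0.6: the halt rate is 46.1% at 10 per group, 45.1% at 30 and 44.5% at 40. The cut-off causes the risk.

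**Other forms of rule.** Requiring 80% conditional power under the current trend halts 42% at d = 0.6 (36% of finally significant trials). Lowering that requirement to 20% halts 11% of finally significant trials, but then only 51% of nulls.

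**The case against.** The strongest reply is that a positive trial is not defined in the disputed sentence, and that the simulations ran from d = 0 to 1.6. If positive means any effect from 0.6 to 1.6 with equal weight, the stated rule halts roughly 12 to 13% of the trials that would have been significant, close to the stated figure. But the weights and the range are assumptions found nowhere in the article, while the same paragraph and the Fig. 3 legend both name d = 0.6. Pooling over the whole simulated range from d = 0 gives 18% of finally significant trials, or 13% as a joint probability.

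A slip of wording is also possible: at d = 0, about 11% of trials are continued and end non-significant. That is a different error from the one the sentence describes, so the sentence would still be wrong.

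Fig. 3 is not available here and may show the correct rate at d = 0.6. That would reduce the matter to a text error. The disputed number and the rule behind it are nonetheless both in the text.

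Two points stand. First, on the article's own false-negative definition the rate is 40%, so the understatement is four-fold on that reading and about 4.6-fold only when all trials at d = 0.6 are counted. Second, the 10% is not the sole support for 15 per group: the Fig. 3 legend argues from diminishing returns, and the flat halt rate at d = 0.6 agrees that a larger interim would not lower this risk much. The futility cut-offs are also fixed in advance, so no stopping decision uses the 10%.

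**Conclusion.** The stated risk of about 10% is wrong as written. At d = 0.6 the stated rule halts 46% of trials at interim 1, or 40% of those that would have been significant at 50 per group. The chance of ending with a significant result falls from 84.5% to 51%. At interims 2 and 3 the halt rate at d = 0.6 rises to about 51% and 58%. The companion claim about null effects is sound (87%).

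This rests on normal data with equal SDs, on the published cut-offs applied to the observed d, and on 15 per group at each interim. If controls accumulate beyond 15 by the later interims, the rates there rise slightly: with 30 controls against 15 they would be 52% and 59%. It also takes a positive trial to mean d = 0.6, the only non-null effect the paragraph names.

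The error does not argue for a different interim size. It means that a futility stop under this rule is weak evidence against a clinically relevant effect.

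**What to change.** In the Discussion (Simulations), define a positive trial as d = 0.6 and replace the 10% with the actual rates: about 46% of such trials halted at interim 1, or 40% of those that would have been significant at 50 per group, and about 51% and 58% of all such trials at interims 2 and 3. Rerun the simulation behind Fig. 3 for all three stages, each with its own cut-off and final size, and show the halt rates at d = 0 and d = 0.6 side by side. Describe 15 per group with its cut-off as a screening choice that accepts this risk, and say that a futility stop does not rule out an effect of clinical interest.

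The cost is one simulation rerun and some text edits, and a less favourable stated risk. The sample size does not change.

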### Other adaptive designs

There are many varieties of adaptive design which could be applied to RbG studies. We chose to run sequential allele groups in our recruitment which was ordered on prior knowledge, allele frequency and confidence in the assocations. Where there is equal confidence in the alleles, an alternative adaptive design could recruit from all allele groups, and after interim adapt recruitment to a single group which creates a larger cohort to recruit from at the start of the study.

## Concluding remarks

The novel approach to a recall by genotype study presented herein will allow efficient assessment of the contribution of common SNPs to pain sensitivity and offers an alternative approach to understanding the polygenic contributions to this complex and heterogeneous phenotype. In addition, this approach prevents unnecessary testing of individuals where there is unlikely to be an effect on the phenotype of interest, which is an important ethical consideration. We suggest that this approaches’ ability to maximise both exploratory potential and resources can be applied across all RbG settings.

## Data Availability

Data collected as part of this study will be available on request to the ALSPAC executive committee ([contact]). The ALSPAC data management plan (available here: http://www.bristol.ac.uk/alspac/researchers/data-access/) describes in detail the policy regarding data sharing, which is through a system of managed open access. Code used both in the work presented herein and in the statistical analysis itself will be made available from the corresponding author ([contact]) on reasonable request.

## Abbreviations

AITC: Allyl isothiocyanate
ALSPAC: Avon longitudinal study of parents and children
CFA: Coal fly ash
DFNS: German research network on neuropathic pain (Deutsche Forschungsverbund Neuropathischer Schmerz)
FDA: Food and Drug Administration
FLPI: Full-field laser perfusion imaging
GWAS: Genome wide association study
HEK: Human embryonic kidney cells
HPT: Heat pain threshold
IMMPACT: Initiative on methods, measurement, and pain assessment in clinical trials
MAF: Minor allele frequency
QST: Quantitative sensory testing
RbG: Recall by genotype
SNPs: Single nucleotide polymorphisms
TRPA1: Transient receptor potential A1
